**Figure 4. F4:**
[figure not shown]
System and equipment used to send sham educational intervention to control participants by SMS text messaging (once during week 4 and once during week 8 of the intervention period).

**Figure 5. F5:**
[figure not shown]
System and equipment used by the control participants every day during weeks 11 and 12 of the intervention period. AI: artificial intelligence.

On the first 3 days during week 10, at 11 AM, study participants will receive an SMS text message containing a survey link for a TPB questionnaire (via Jotform). On day 1 of week 10, study participants will receive a TPB questionnaire about increasing fiber intake. On day 2, they will receive a TPB questionnaire about reducing salt intake. On day 3, they will receive a TPB questionnaire about reducing saturated fat intake. Study participants are required to complete these surveys at home or any convenient location with an internet connection.

The flow of interaction between the intervention participant, the app interface, the backend system, and the AI server is as follows, as illustrated in Figure 5: the control participant logs meal via “Snap a meal” function or “Chat a meal” function in MealLog app during week 11 and week 12 of the intervention period (Step 1). Data provided by the participant is sent to the AI servers (Step 2). The AI servers process the uploaded meal photo or chatbot interaction and generate information on fiber, energy, carbohydrates, protein, fat, and salt amount (Step 3). Once the AI server completes processing, the app receives relevant feedback and data generated by AI. This feedback is not visible to the user within the app interface (Step 4). The mobile app then securely transmits the feedback to the backend system via internet connection using a highly encrypted API stored within the app (Step 5).

#### Study Events

This study includes 5 events (E0-E4), a 2-week run-in period, a 12-week intervention period, and a 12-week observation period. Study participant experience and data collected in different stages of the study are described in Table 3.

**Table 3. T3:** Study events spanning approximately 26 weeks.

Event	Time	Key activities	
E0	Preliminary study enrollment	Participant experience: obtain consent to participate in study. Data collected: Patient background^a^, vital signs^b^, hematological tests^c^, biochemical tests^d^, urinalysis^e^, medication status survey, and the transtheoretical model (TTM) questionnaire for dietary behavior change^f^.	
Run-in period	From E0 for 2 weeks	Participant experience: Log meals with MealLog app Data collected: Number of days with at least 2 logged eating occasions (main meals or snacks), total fiber intake per day (grams), average fiber intake (excluding days with only 0 or 1 logged meal), theory of planned behavior (TPB) questionnaire for dietary fiber intake^g^, TPB questionnaire for salt intake^g^, and TPB questionnaire for saturated fat intake^g^.	
E1	At the time of official study enrollment	Intervention group: Participant experience: Download FiberMore and receive educational handout on dietary fiber intake. Data collected: Medication status and system defects.	
		Control group: Participant experience: Receive educational handout on salt reduction. Data collected: Medication status and system defects.	
Intervention period	From E1 for 12 weeks	Intervention group: Participant experience: Interact with FiberMore. Data collected: The number and percentage of days fiber goal is met out of 7 days, the number and percentage of implemented coping strategies per week, the average estimate of fiber intake per day (excluding days with only 0 or 1 logged meal), and the average estimate of energy intake per day (excluding days with only 0 or 1 logged meal).	
		Control group: Participant experience: Record salt reduction efforts in a paper diary (sham intervention), receive 1-time educational weblink on salt reduction via an SMS text message during week 4 and week 8, and use MealLog to log meals during week 11 and week 12. Data collected: During week 11 and week 12—the average estimate of fiber intake per day (excluding days with only 0 or 1 logged meal) and the average estimate of energy intake per day (excluding days with only 0 or 1 logged meal).	
E2	Week 10 of the intervention period	Participant experience: receive a survey link of TPB questionnaires about dietary fiber, salt, and saturated fat on specified day via SMS text messages.^g^ Data collected: TPB questionnaire for dietary fiber intake, TPB questionnaire for salt intake, and TPB questionnaire for saturated fat intake.	
E3	End of 12 weeks from E1 (end of the intervention period)	Participant experience: attend regular outpatient clinic appointment and attend E3 meeting with a clinical research coordinator (CRC). Data collected: vital signs, hematological examination, biochemical tests, urinalysis, medication status, system defect report, TTM questionnaire for dietary behavior change, and a survey on the participants’ satisfaction and perceived usefulness of the intervention.	
E4	End of 24 weeks from E1 (end of the observation period)	Participant experience: attend regular outpatient clinic appointment, attend E4 meeting with CRC, receive survey link of TPB questionnaires for dietary fiber, salt, and saturated fat on specified day via SMS text messages. Data collected: Vital signs, hematological examination, biochemical tests, urinalysis, medication status, and TTM questionnaire for dietary behavior change; TPB questionnaire for dietary fiber intake; TPB questionnaire for salt intake; TPB questionnaire for saturated fat intake; and a survey on the intention to improve eating habits using a generative artificial intelligence (AI)-enabled app.	

a Definitions related to observation, investigation, and reporting items: Patient background: (1) Via self-administered questionnaire: Highest education level, annual income, marital status, living arrangement, employment status, meal arrangement methods, control over meal ingredients and menu, level of daily physical activity; (2) Via medical record: Age, sex, date of diabetes diagnosis, smoking and alcohol consumption at the time of consent acquisition; the presence of macrovascular disease, diabetic retinopathy, periodontal disease, tinea pedis, and diabetic neuropathy; and other medical history.

b Vital signs: Body height, body weight, and systolic and diastolic blood pressure.

c Hematological tests (Performed at least a week before each time point): hemoglobin level.

d Biochemical tests (performed at least a week before each time point): estimate glomerular filtration rate (eGFR), creatinine, fasting blood glucose, HbA_1c_, low-density lipoprotein cholesterol (LDL-C), high-density lipoprotein cholesterol (HDL-C), triglycerides, albumin, blood urea nitrogen (BUN), and potassium.

e Urinalysis (performed at least a week before each time point): Urine protein and urine-albumin-creatine ratio (UACR).

f Transtheoretical model (TTM) questionnaire: Measure the 5 stages of dietary behavior change in TTM: Precontemplation, contemplation, preparation, action, and maintenance. Amount of dietary fiber intake: artificial intelligence (AI) assessment of dietary fiber intake via meals logged onto the app.

g The theory of planned behavior (TPB) questionnaire: Measure attitude, subjective norms, perceived behavioral control, and intention to improve dietary behavior.

### Study Outcomes

#### Primary Outcome

The primary outcome of this study is the between-group difference in the change in daily intake of dietary fiber from the time of run-in to the end of the intervention period.

#### Secondary Outcomes

Secondary outcomes (see Table 4) include clinical and health measures, measurements of behavior changes, engagement measures with intervention features, and assessments of participants’ satisfaction and perceived usefulness of the intervention. We will also assess the occurrence of adverse events via patient interviews.

**Table 4. T4:** Secondary outcome measures.

Measurements	Outcomes
Difference in changes	HbA_1c_ (%)^a^ Weight (kg)^a^ BMI (kg/m^2^)^a^ Systolic and diastolic blood pressure (mmHg)^a^ Estimate glomerular filtration rate (eGFR; ml/min/1.73m2)^a^ Fasting blood glucose (mg/dL)^a^ Low-density lipoprotein cholesterol (LDL-C; mg/dL)^a^ High-density lipoprotein cholesterol (HDL-C; mg/dL)^a^ Triglyceride (mg/dL)^a^ Theory of planned behavior (TPB) elements for dietary fiber, salt, and saturated fat intake (attitude, subjective norm, perceived behavioral control, and intention).^b^
Difference in proportions	Transtheoretical model (TTM) stage of change questionnaire for dietary behavior.^a^ Changes in antidiabetic drugs since consent was obtained (intensified, unchanged, and weakened).^a^ Usage of each antidiabetic drug.^c^
Measured values	Average estimate of fiber intake per day.^d^ Average estimate of energy intake per day.^d^ Number and percentage of days fiber goal is met out of 7 days.^d^ Number and percentage of implemented solutions in a week.^d^ Survey on participants’ satisfaction and perceived usefulness of the intervention.^e^ Percentage of patients with HbA_1c_ less than 7%.^f^ Survey on intention to improve eating habits using a generative artificial intelligence (AI)-enabled app^g^

a Difference in change from the time consent was obtained to the end of the intervention period (12 weeks) and to the end of the observation period (24 weeks).

b Difference in change from the time of run-in to the end of 10 weeks and to the end of the observation period (24 weeks).

c Calculated at the time of consent acquisition, at the time of official study enrollment, after the end of the intervention period, and after the end of the observation period.

d Evaluated weekly from week 1 to 12 for the intervention group.

e Percentages of responses for each option on the Likert scale and for the Yes or No scale will be calculated after the end of the intervention period for the intervention group and control group.

f Evaluated at the end of week 12 and week 24 for both intervention group and control group.

g Percentages of responses for each option on the Likert scale will be calculated after the end of the observation period for the intervention group.

### Sample Size Consideration

The primary outcome is the difference between the intervention group and the control group in the change in mean daily dietary fiber intake from the time of study enrollment to the end of the intervention period. We desired to detect a between-group difference in the mean change of 7 g of dietary fiber, drawing from a meta-analysis, which demonstrated a 9% risk reduction of cardiovascular disease events for 7 g increase in daily dietary fiber intake [47]. A previous RCT reported a 7.9 g/day increase in fiber intake at 3 months in the high-fiber group, supporting the use of a 7 g/day between-group difference as a realistic and meaningful target [33].

Based on the findings from a previous nutritional intervention research in Japan [48], we assumed a common SD of 9.85 g for the difference in dietary fiber change across both groups. Using a 2-sided significance level of 5% and a power of 80%, the required sample size calculated based on an independent *t* test is 33 participants per group. A study conducted in a similar population, which followed a similar study structure with a 2-week run-in phase, a 12-week intervention phase, and a subsequent 12-week observation phase by our research team showed minimal to no dropout throughout the study duration [49]. Nevertheless, as a conservative estimate to account for potential attrition, we aimed to enroll a minimum of 70 participants. The 2-week run-in phase also ensures that we enroll the participants who are able to use the app as instructed, thus minimizing drop-out risk.

Based on the findings from previous studies implemented in our research lab, we estimate a 10% dropout rate between preliminary and official study enrollment. Therefore, the target recruitment number for the preliminary study enrollment has been set at 77 participants.

### Statistical Analysis Plan

In this study, we define 3 analysis populations: the full analysis set (FAS), the per protocol set (PPS), and the safety analysis set (SAS). The FAS is defined by all the study participants who had at least one primary outcome or secondary outcome obtained after randomization. We will follow the intention-to-treat (ITT) principle and analyze data based on the assigned group in the FAS analysis. The PPS is the FAS population with exclusion of patients who were found to have serious violations of the provisions of the research protocol:

Violation of inclusion and exclusion criteriaStudy participants who log fewer than 2 meals per day on more than 7 days within any of the following 2-week intervals during the intervention period: Weeks 1‐2, 3‐4, 5‐6, 7‐8, 9‐10, 11‐12, or 13‐14.In the event of a medical condition that makes dietary fiber intake inappropriate for the study participants,

Major deviations from other provisions of the study protocol will be assessed through a blinded review process. The blinded review will be conducted according to the following procedures: assessment of whether individual participants or specific measurement data should be excluded from the PPS or FAS; evaluation of participants with significant protocol deviations to determine whether exclusion is warranted; and examination of efficacy outcomes, including consideration of potential variable transformations and identification of outliers.

The safety analysis set is the set of all patients who used either MealLog or FiberMore at least once after randomization. In the safety analysis using the SAS, we will analyze data based on the intervention actually used by patients regardless of allocation. The FAS will be the primary analysis population, and the PPS will provide supportive results. All safety analyses will be conducted in the SAS. Data on patients’ characteristics will be presented as mean, minimum, SD, 25th percentile, median, 75th percentile, and maximum for continuous variables and as frequency and proportion for categorical variables.

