## Methods

### Study Overview

This is a single-blind, parallel-group pilot randomized controlled trial targeting patients with T2D who consume less than 20 g of dietary fiber per day on average. Following a 2-week run-in period, study participants will undergo a 12-week intervention period, followed by a 12-week observation period, making the total study duration 26 weeks (with a maximum of 30 weeks, including allowable ranges in clinic visits; see Figure 1).

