**Figure 1. F1:**
[figure not shown]
Overview of study timeline.

The intervention group is given access to an AI-powered dietary fiber intake support system named “FiberMore” throughout the 12-week intervention period. The intervention offers several features, including fiber content assessment of meals through meal photos and interacting with a chatbot, tailored feedback on logged meals, personalized fiber goal setting, barrier identification to eat more fiber and strategies (solutions) to overcome them, emotional attitude assessment toward eating more fiber, and access to educational information on dietary fiber via a chatbot.

The study will use a “sham intervention” related to dietary behavior change as control [41]. The main purpose of using a sham intervention is to achieve participant blinding and to control for the Hawthorne effect of receiving an intervention [42]. Salt reduction education aligns with dietary recommendation for T2D management. The educational content specifically focuses on reducing sodium intake through cooking methods and seasoning practices, without targeting food choices related to dietary fiber. The control group receives educational intervention on salt reduction at 3 time points: at official study enrollment (via an educational handout), at week 4 (through web-based educational information delivered via SMS), and at week 8 (through web-based educational information delivered via SMS). Additionally, participants in the control group will document their salt reduction efforts in a paper diary throughout the intervention period. They will use the meal logging app “MealLog” to record their meals at week 11 and 12, which allows for meal logging without providing any feedback or dietary intervention.

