#### The Control Condition

After randomization, the control group will receive an educational handout on salt intake reduction as well as a paper diary to record their efforts in reducing salt intake. They are encouraged to record any small effort to reduce salt intake in the diary on a daily basis. They will also receive web-based educational information via SMS text message once during week 4 and once during week 8 (see Figure 4). On the last day of week 10, the control group will receive SMS text message reminders from the research office to use MealLog to log their meals for 14 days during week 11 and week 12 (see Figure 5).

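### The per-protocol logging rule has no limit by arm, so read literally it removes every control who follows the logging schedule and leaves no between-group per-protocol comparison

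*Protocol article*

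**What the plan says.** The Statistical Analysis Plan section makes the full analysis set (FAS) primary and the PPS supportive. The PPS is the FAS without patients who seriously violated the protocol. One listed violation concerns "participants who log fewer than 2 meals per day on more than 7 days within any of the following 2-week intervals", and the intervals are those "during the intervention period: Weeks 1‐2, 3‐4, 5‐6, 7‐8, 9‐10, 11‐12, or 13‐14". The sentence does not mention arm.

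The control schedule appears in three places and is consistent:

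- Study Overview: controls use the MealLog app to "record their meals at week 11 and 12, which allows for meal logging without providing any feedback or dietary intervention", and "participants in the control group will document their salt reduction efforts in a paper diary throughout the intervention period".
- The Control Condition: a reminder on the last day of week 10 asks them "to use MealLog to log their meals for 14 days during week 11 and week 12".
- Study Events, Table 3: controls "use MealLog to log meals during week 11 and week 12".

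On duration, Study Overview states that "study participants will undergo a 12-week intervention period, followed by a 12-week observation period". It gives a total of 26 weeks, or up to 30 weeks once allowable visit ranges are included.

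**The concern.** A per-protocol rule should remove people who departed from what they were asked to do. This one counts days without meal logging in weeks when one arm is not asked to log meals. The salt diary that controls keep throughout records effort at salt reduction; it is not a meal log and cannot satisfy the rule. Non-logging in weeks 1-10 is therefore built into the control condition, yet the text counts it as a serious violation.

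At stake is whether the supportive analysis can be produced as written. If it cannot, someone must decide later how to repair the rule. A repair chosen once data are available would turn the PPS into a post hoc population. The blinded review does not clearly settle the matter: the text gives it deviations from other provisions, and logging records from weeks 1-10 would tend to reveal the arm, because only FiberMore users are scheduled to log then.

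**Working it through.** The plan gives no expected PPS size, so there is no figure to reproduce. The sample size of 33 per group does not enter this point.

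**Inputs**

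- Exclusion: more than 7 days with fewer than 2 logged meals, in any one listed interval of 14 days (Statistical Analysis Plan).
- Intervals: weeks 1-2, 3-4, 5-6, 7-8, 9-10, 11-12 and 13-14 (same section).
- Control logging: weeks 11-12 only (Study Overview; The Control Condition; Table 3).
- Intervention logging: FiberMore throughout weeks 1-12 (Study Overview).
- Allocation 1:1 (Official Study Enrollment and Randomization); 72 randomized by September 22, 2025 (Results).

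**Count for a participant who logs fully whenever scheduled, and only then**

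Low-logging days in an interval = 7 × (number of its weeks without scheduled logging). Exclusion follows if this exceeds 7.

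| Interval | Control | Intervention |
|---|---|---|
| Weeks 1-2 | 14, fails | 0 |
| Weeks 3-4 | 14, fails | 0 |
| Weeks 5-6 | 14, fails | 0 |
| Weeks 7-8 | 14, fails | 0 |
| Weeks 9-10 | 14, fails | 0 |
| Weeks 11-12 | 0 | 0 |
| Weeks 13-14, if counted | 14, fails | 14, fails |

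A compliant control fails five intervals within the 12 weeks, or six if weeks 13-14 count. One is enough, so the PPS keeps 0% of such controls. At 1:1, 72 / 2 = about 36 participants. A control could stay in only by logging, unasked, 2 or more meals on at least 14 − 7 = 7 days of every interval in weeks 1-10.

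**Count after limiting the rule to scheduled logging**

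Control, weeks 11-12: 0 low days, kept. Intervention, weeks 1-2 to 11-12: 0 low days in each of six intervals, kept. Both arms retain their compliant participants.

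**Asymmetry that remains after that repair**

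The intervention arm must pass six windows and controls one. The documents give no failure rate, so assume a probability p of failing any one window, equal in both arms. With independent windows, the intervention arm loses 1 − (1 − p)^6 and controls lose p:

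- p = 2%: 1 − 0.98^6 = 11.4% against 2%
- p = 5%: 1 − 0.95^6 = 26.5% against 5%
- p = 10%: 1 − 0.90^6 = 46.9% against 10%

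If the same people failed every window, both arms would lose p. The truth probably lies between. These figures show unequal selection, not bias in grams of fiber.

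**The case against.** The strongest reply is that the rule sits under a clause about serious violations of the protocol. A control who logs nothing in weeks 1-10 violates nothing, so the rule should be taken to bind controls in weeks 11-12 only. That is probably what was meant. But the rule has an explicit threshold and seven named intervals, and no wording ties it to scheduled logging. This is a stated rule that gives a wrong result, not detail left to a fuller document.

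A reader might infer from weeks 13-14 that the intervention arm is emptied too. The documents do not support stating this flatly. The rule speaks of intervals within the intervention period, which for someone finishing on time ends at week 12, and the 30-week maximum in Study Overview makes a visit-window extension a plausible reason for the entry. What stands is that the entry does not fit a 12-week period and is not explained.

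A reader might also infer that a repaired PPS would overstate the FiberMore effect by a definite amount. That needs the share of users who fail and the fiber change in those who fail, those who pass and controls; the documents give none of these. Selection on adherence after randomization is a known limit of any PPS, and one reason this one is only supportive. It would also be wrong to say that controls would be unselected, since under the natural reading they must still meet the weeks 11-12 rule.

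**Conclusion.** The point holds for the PPS as worded. Applied literally, the rule removes every control who keeps to the logging schedule, about 36 of 72 randomized, and leaves no between-group PPS estimate. This rests on the rule having no arm limit and on controls not logging meals unasked in weeks 1-10.

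It should not be read as a threat to the main result. The primary analysis of covariance uses the FAS, and its fiber change compares weeks 11-12 with run-in, when both arms log. Nor can it be said that the PPS is the trial's only supporting analysis, because the article condenses a fuller protocol that is not shown. The defect is confined to one supportive population, but it is definite and cheap to correct.

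**What to change.** Before database lock:

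1. Apply the logging exclusion only to intervals in which the participant's arm is scheduled to log: weeks 11-12 for controls, and the six intervals from weeks 1-2 to 11-12 for the intervention arm.
2. Delete weeks 13-14, or restrict them to participants whose intervention period is extended, and say so.
3. Also report a PPS version with one requirement for both arms: no more than 7 of 14 days with fewer than 2 logged meals in weeks 11-12.
4. Interpret the by-arm PPS in light of its six windows against one.

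Both versions are worth having. The by-arm rule keeps the meaning of adherence to a 12-week intervention but selects the arms unequally. The common rule treats the arms alike in the endpoint window, but would count someone who ignored FiberMore until week 11 as per protocol. The cost is one sentence and one extra supportive analysis; the FAS, the sample size and data collection do not change.

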#### The Intervention Condition

A CRC will assist study participants assigned to the intervention group with downloading FiberMore onto their smartphones and input the initial fiber goal of the study participants to the backend system (refer to Table 2 for determination of the initial goal). The CRC will also assist the study participants to identify 1 barrier on increasing fiber intake and its corresponding solution via the “Barrier and Solution” chatbot within FiberMore. The CRC will also provide guidance and demonstration on using the intervention features of FiberMore.

The CRC will give study participants a handout on the benefits of increasing fiber intake as well as general tips and examples about eating more fiber. As some study participants depend on their family for meal preparation, the CRC will encourage the study participant to share the educational handout with their family members and communicate the weekly fiber goal as well as the feedback obtained from FiberMore with their family or person preparing their meals.

On the first three days during week 10, at 11 AM, study participants will receive an SMS text message containing a survey link for a TPB questionnaire (via Jotform). On day 1 of week 10, study participants will receive a TPB questionnaire about increasing fiber intake. On day 2, they will receive a TPB questionnaire about reducing salt intake. On day 3, they will receive a TPB questionnaire about reducing saturated fat intake. Study participants are required to complete these surveys at home or any convenient location with an internet connection.

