We will also calculate the percentage of responses for each option on the Likert scale and for the “Yes or No” scale in “Survey on participants’ satisfaction and perceived usefulness of the intervention” at the end of the intervention period for both intervention group and control group. For the “Survey on intention to improve eating habits using a Generative AI-enabled app”, we will calculate the percentage of responses for each option on the Likert scale at the end of the observation period for the intervention group.

As part of our exploratory analysis, we will assess the reliability of the TPB questionnaire using the Cronbach α coefficient. Additionally, we will conduct multivariate regression analyses to examine various associations related to the TPB constructs. Specifically, we will investigate the relationship between changes in intention (INT) to increase fiber intake and changes in fiber intake outcomes both between and within groups. Furthermore, we will analyze the associations between changes in attitude (ATT), subjective norms (SN), and PBC with changes in intention to increase fiber intake, as well as the relationship between changes in PBC and changes in fiber intake outcomes at both the between-group and within-group levels. The impact of the intervention on INT via ATT, SN, and PBC will be evaluated through mediation analysis.

We will calculate the frequency and weekly percentages of the following measurements during the intervention period in the intervention: number and percentage of days fiber goal is met out of 7 days, the number and percentage of implemented solutions in a week, the average weekly fiber change in the intervention group from run-in, and the average weekly energy change in the intervention group from run-in. We will also evaluate the effects of changes in dietary fiber intake on changes in BMI and HbA_1c_ using the Pearson correlation test and simple regression analysis.

We will perform a statistical analysis of safety outcomes by calculating the number and percentage of individuals who experience adverse events during run-in, intervention, and observation periods. During the intervention and observation periods, data will be compiled separately for the intervention and control group, and the percentages will be compared between groups using the Fisher exact test.

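### Safety-set entry depends on arm: intervention participants qualify at E1, but controls have no scheduled qualifying app use until weeks 11-12, so early-stopping or non-logging controls can drop out of every safety analysis

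*Protocol article*

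**What the plan says.** The protocol article, under Statistical Analysis Plan, sets one condition for the safety set: "The safety analysis set is the set of all patients who used either MealLog or FiberMore at least once after randomization". It then fixes the scope, "All safety analyses will be conducted in the SAS", and the grouping, "we will analyze data based on the intervention actually used by patients regardless of allocation".

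The two arms meet that condition at different times.

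- **Intervention arm** (The Intervention Condition): at E1 a research coordinator helps participants "assigned to the intervention group with downloading FiberMore onto their smartphones". At the same visit they choose a barrier and a solution in the app.
- **Control arm** (The Control Condition): after randomization "the control group will receive an educational handout on salt intake reduction as well as a paper diary". Web-based salt education follows by SMS in weeks 4 and 8. On the last day of week 10 controls are reminded "to use MealLog to log their meals for 14 days during week 11 and week 12". Study Overview and Table 3 show the same schedule.

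Adverse events are assessed by patient interview (Secondary Outcomes). If a participant withdraws after randomization, the data collected until then are kept (Ethical Considerations). The safety analysis (Secondary Outcomes Analysis) consists of "calculating the number and percentage of individuals who experience adverse events during run-in, intervention, and observation periods", with a Fisher exact test between groups for the intervention and observation periods.

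**The concern.** A safety set should admit people by a rule that works alike in both arms and does not depend on what happens to them afterwards. Here an intervention participant is in the set from the first visit. A control has no scheduled way into it for the first 10 of the 12 intervention weeks.

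Two kinds of control are at risk of exclusion: those who stop in weeks 1 to 10 for any reason, including an adverse event, and those who stay but log nothing in weeks 11 and 12. Their events are known to the trial, because they come from interviews and not from the app, and the data are retained. The definition sets aside information that the trial already holds.

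At stake is the comparability of the two adverse event percentages. With about 36 participants per arm and probably few events, one or two people can move a percentage visibly. Safety is one of the three things on which the article's conclusions say the trial will give evidence.

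**Working it through.** **1. Plan's own figure.** The protocol gives no size for the safety set, so there is nothing to reproduce on this point. The sample size matters only for the dropout allowance. A difference of 7 g, an SD of 9.85 g, two-sided 5% and 80% power give 32.07 per group by the *t* test, rounded up to the stated 33.

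**2. Who qualifies, and when.**

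| Situation after randomization | Intervention | Control |
|---|---|---|
| Attends E1, then stops in weeks 1-10 | In the set (FiberMore used at E1) | Out, unless MealLog was used unprompted |
| Stays, but logs nothing in weeks 11-12 | In | Out, unless MealLog was used unprompted |
| Logs one meal in week 11 | In | In |

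**3. Cross-check with the full analysis set.** That set takes anyone with at least one primary or secondary outcome after randomization. A control with only the week 10 theory-of-planned-behavior questionnaire, or with HbA1c at E3 but no logging, is in the efficacy set and outside the safety set. For such controls the safety set is the narrower of the two.

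**4. Number of controls likely to be affected.** The protocol needs 2 × 33 = 66 and enrolls at least 70. The allowance is 70 − 66 = 4, which is 4/70 = 5.7%, or about 2 per arm over the whole study. The protocol expects minimal or no dropout.

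**5. Effect on the comparison (assumed event counts).** The 72 randomized at 1:1 give about 36 per arm. Assume 8 participants with events in each arm, so the true rates are 8/36 = 22.2% and the true difference is 0. Let *k* controls leave the set, *a* of them with events. The control rate becomes (8 − *a*)/(36 − *k*).

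| *k* | All leavers had events (*a* = *k*) | Intervention minus control | Leavers event-free (*a* = 0) | Intervention minus control |
|---|---|---|---|---|
| 2 | 6/34 = 17.6% | +4.6 points | 8/34 = 23.5% | −1.3 points |
| 3 | 5/33 = 15.2% | +7.1 points | 8/33 = 24.2% | −2.0 points |
| 4 | 4/32 = 12.5% | +9.7 points | 8/32 = 25.0% | −2.8 points |

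The *a* = *k* columns are the worst case in one direction. If leaving is unrelated to events, the expected control rate does not change. The Fisher *p* values for the worst case are 0.77, 0.55 and 0.35, so the test result would not change. The percentages would.

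With all randomized controls counted, the difference is 0 in every row.

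**6. Run-in.** The plan promises run-in adverse event percentages, but it places all safety analyses in a set that requires app use after randomization. A person with a run-in event who is never randomized cannot be counted.

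**The case against.** Several objections limit the point, and most of them stand.

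- **Controls have MealLog throughout.** It is installed at consent and used in run-in, and no removal is stated. A reader might infer that controls get the app only in week 11 and that early leavers can never enter the set. The documents do not support that: week 11 is the first *scheduled* use after randomization, and unprompted use would qualify. Entry would then rest on chance, so the asymmetry remains.
- **The direction is not fixed.** A reader might infer that the definition makes FiberMore look less safe by construction. That holds only if early-leaving controls have more events than those who stay. Event-free leavers shift the comparison the other way.
- **The larger figures need more dropout than planned.** Losing 3 or 4 of 36 controls before week 11 exceeds the protocol's own allowance of about 2 per arm.
- **MealLog is not named as the control intervention.** App use decides membership; grouping by the intervention used is a separate sentence. It would be too strong to say that the plan equates the two.
- **The run-in issue is separate and small.** Run-in has no between-group comparison. At the data cut 81 − 72 = 9 recruited participants were not randomized, but the text gives no reason for this, so nine is not a count of people whose events are lost.
- **The setting is a pilot.** Adverse events are among the secondary outcomes, which are to be read as exploratory, and the primary analysis uses the full analysis set.

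None of this gives early-stopping or non-logging controls a dependable route into the safety set.

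**Conclusion.** The point holds. Entry to the safety set depends on arm, and in the control arm alone it is conditioned on staying to week 11 and logging. The resulting bias in the adverse event comparison can go either way; it makes FiberMore look less safe if controls stop because of events.

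The plausible size is the loss of two controls or fewer. On the assumed 8/36 per arm, two losses mean a spurious difference between +4.6 points (both had events) and −1.3 points (neither did). Differences up to 9.7 points need four early-stopping controls, all with events, and are a worst case. The 36 per arm follow from 72 randomized at 1:1. The event counts and the number of leavers are assumptions, because the document gives neither an adverse event rate nor dropout by arm.

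This should be fixed. It does not threaten the primary result.

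**What to change.** Define the safety set as all randomized participants who received any allocated material at E1 (FiberMore or the fiber handout; the salt handout or the diary), grouped by the intervention received. Entry is then decided at the same visit in both arms and no longer depends on reaching week 11.

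As a minor addition, summarise run-in adverse events descriptively in consented participants who used MealLog and whose data are retained. The restriction is needed because Ethical Considerations says that data are discarded when consent is withdrawn before randomization.

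The cost is a sentence or two of wording before analysis. No new data are needed, since adverse events come from interviews and data up to withdrawal after randomization are kept.
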